### Couple Dissolution

If a couple does not remain together throughout the follow-up period, HIV-positive partners will be retained in the study for the full 2-year follow-up period, while HIV-negative partners will return for one more follow-up visit and then will be censored from the cohort. If an HIV-positive partner in the intervention arm obtains a new partner who is eligible for the study, that partner will be invited to attend further follow-up visits, to continue providing CHTC to the original positive partner with the new partner. This new partner will participate in surveys, sample collections, counseling sessions and bi-monthly phone calls. At the Boston site, new negative partners are also invited to enroll if they are in the control arm.

### Biomedical Measures

For HIV-negative partners, HIV sero-status is tested at each study assessment. For HIV-positive partners, viral load and ART levels are measured at each study assessment and collected via dried blood spots. All participants are tested for syphilis at each study assessment in the Atlanta and Chicago sites. Budgetary constraints prevented testing for other STIs, as well as syphilis testing, in the Boston site.

### Outcomes

The primary outcomes are the HIV-positive partner’s engagement in HIV care and his achievement of viral suppression. Engagement in care is conceptualized as also including linkage to care and retention in HIV care. For HIV-positive partners who report no engagement in HIV care at baseline, linkage to care is defined as attending at least one clinical care appointment, having at least one CD4 test performed, and having at least one viral load test performed within 3 months of the baseline visit. Retention in care is measured by determining participation in continuous care; that is, at least two or more routine HIV visits at least three months apart, receiving two or more CD4 tests, and receiving two or more viral load tests within a 12-month period [58]. At each study visit, a blood draw will be conducted to provide a measure of the HIV-positive partner’s viral load and to test levels of ART. To supplement the viral load and ART-level biological markers, self-reported ART adherence is collected in each of the surveys. The AIDS Clinical Trial Group (ACTG) questionnaire includes items measuring adherence to medications for the past 4 days, adherence to scheduled instructions during the last weekend, and when any medication was last skipped. The questionnaire responses are weighted to calculate an adherence level from 0-100. The surveys also measure barriers to adherence via a 24-item scale based on the ACTG assessment for barriers to adherence to ART [59]. Participants are asked to note (using a scale ranging from *never* to *often*) if they missed their HIV medication over the past month for one of the provided reasons.

As secondary outcomes, the study measures sexual risk-taking and formation, and adherence of sexual agreements. For sexual agreements, participants are asked which of the following best describes their current sexual agreement with their main partner: (1) *both of us cannot have sex with outside partners*, (2) *we can have sex with outside partners, without any conditions or restrictions*, (3) *we can have sex with outside partners, but with some conditions or restrictions*, and (4) *we do not have an agreement*. Comparison of individual data will allow identification of discordant agreements. Participants will be asked if they have broken this agreement and whether this breakage was disclosed to their partner. To assess sexual behavior, measures adapted from the National HIV Behavioral Surveillance (NHBS) behavioral inventory collect information both on sexual behaviors with the main sex partner in the 3 months before the interview, and on sexual behaviors with all sex partners outside the relationship. For sex with the main partner, men are asked to estimate the number of anal sex acts with the main partner and the number of those acts that were condom-protected. For each partner outside the relationship, men are asked a series of questions to include characteristics of the outside partner, HIV status (if known), whether the sex outside the relationship was disclosed to the main partner, the number and type of sex acts, and the proportion of those sex acts that were protected by condoms. Additional outcomes assessed are centered on Couple’s Interdependence Theory.

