## Methods

### Design

The research activities involve a prospective RCT of approximately 165 venue- and clinic-recruited sero-discordant male couples (330 individuals: 165 HIV sero-negative and 165 HIV sero-positive). The study takes place in three cities: Atlanta, GA (study site Emory University); Boston, MA (study site The Fenway Institute); and Chicago, IL (study site Ann & Robert H. Lurie Children’s Hospital of Chicago). Cohort recruitment began in 2015. Couples are followed prospectively for 24 months, with study assessments at baseline, 6, 12, 18, and 24 months.

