### Statistical Analyses

The analysis employs an intent-to-treat analysis design. The percentage of HIV-positive individuals who achieve viral suppression and report being fully engaged in care will be compared across arms, using Chi-square tests for significant difference. Retention in care is measured as the number of 6-month blocks during which at least one clinic visit was attended over the 2-year period following an initial attended visit; the percentage of HIV-positive individuals who report full retention in care (one clinic visit during each 6-month block) and the number of 6-month blocks during which care was received will be compared across study arms, using the appropriate tests for statistical significance. The capability of the intervention to yield longer-lasting effects in adherence endpoints over time will be examined. The visual analog scale data over the course of the study, at baseline and follow-up, will be analyzed using generalized linear models (GLMs) with properly-chosen (based on the distribution of dependent variables) link functions to analyze longitudinal adherence outcome data. The GLMs will be estimated using generalized estimating equations (GEE) with robust standard error estimates, which provide an extension of regression analyses to the cases of correlated or repeated observations and allows for inclusion of both categorical and count-dependent variables, and for appropriate modeling of covariance structures when observations are correlated across time. With appropriate link functions, GLMs can readily handle dependent variables with normal distributions, dichotomous outcomes, count data (Poisson distribution), and over-dispersed or zero-inflated count data (negative binomial models). The models will include the dyadic characteristics scales to examine the extent to which adherence is shaped by relationship functioning.

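### Retention in care, a component of a primary outcome, has two unreconciled definitions, and the block-count version starts its clock at a visit that is not tied to randomisation

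*Protocol article*

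**What the plan says.** The Outcomes section names two primary outcomes for the HIV-positive partner: engagement in HIV care and viral suppression. On the first it states: "Engagement in care is conceptualized as also including linkage to care and retention in HIV care". It then gives retention a yes/no rule: "at least two or more routine HIV visits at least three months apart, receiving two or more CD4 tests", together with "receiving two or more viral load tests within a 12-month period".

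The Statistical Analyses section opens with "The analysis employs an intent-to-treat analysis design" and later gives a different measure: "Retention in care is measured as the number of 6-month blocks during which at least one clinic visit was attended over the 2-year period". The 2-year period is the one "over the 2-year period following an initial attended visit". Two quantities are to be compared between arms: the number of blocks with care, and the percentage with a clinic visit in every block.

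The Design section fixes observation: "Couples are followed prospectively for 24 months". Couples are randomised at the baseline visit (Check-In and Informed Consent; Randomization). Outcomes also expects that some HIV-positive partners will report no HIV care at baseline, though it gives no number.

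**The concern.** The two sections use parallel wording to say how the same construct is measured, and the measures differ. Neither is labelled primary, secondary or supportive. Several later steps depend on the choice. The main chi-square comparison uses full engagement in care, the mediation analysis goes ahead only if the intervention improves it, and Sample Size claims power for it without giving a control rate that could be matched to either definition. Results reports 160 couples randomised and 24-month visits under way, so data are accumulating while two versions of the endpoint remain available.

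The second issue is where the block clock starts. An initial attended visit is not a fixed date relative to randomisation. If it falls after randomisation for some men, the start of their window depends on attendance, which is what the intervention aims to change.

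**Working it through.** The plan gives no figure for this point, so there is none to reproduce. The check sets the two rules side by side, applies them to visit calendars, and follows the clock.

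**Side by side**

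| | Outcomes | Statistical Analyses |
|---|---|---|
| Window | 12 months | 2 years, four 6-month blocks |
| Visits | two or more, at least 3 months apart | one or more per block, no spacing rule |
| CD4 and viral load | two or more of each | none |
| Scale | yes/no | count 0 to 4, plus yes/no |
| Clock start | not stated | an initial attended visit |

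**Meets Outcomes, fails full retention.** Take visits with CD4 and viral load tests at months 1 and 4.5, and none later. The gap is 4.5 − 1 = 3.5 months, inside 12 months, with two tests of each kind, so the Outcomes rule is met. With blocks from baseline (0–6, 6–12, 12–18, 18–24), only the first is filled: 1 of 4. With blocks from month 1 (1–7, 7–13, 13–19, 19–25), again only the first is filled: 1 of 4. The result does not depend on the clock.

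**Meets full retention, fails Outcomes.** Take visits at months 1, 5, 10, 16 and 22 with a single CD4 test in the two years. From baseline, the blocks hold (1, 5), 10, 16 and 22: 4 of 4. From month 1, they hold 5, 10, 16 and 22: again 4 of 4. One CD4 test cannot meet a rule that needs two. Study procedures do not supply the missing test, because Biomedical Measures lists viral load and ART levels for HIV-positive partners but not CD4.

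**Visit timing alone cannot produce the second conflict.** Take one visit from each of four consecutive blocks.
- Visits in adjacent blocks are less than 12 months apart.
- The first falls by month 6 of the window and the fourth no earlier than month 18, so they are at least 18 − 6 = 12 months apart.
- If all three gaps were under 3 months, the total would be under 9 months, which is a contradiction.
- So at least one pair is 3 or more months apart within some 12-month period.

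The reverse conflict therefore needs missing laboratory tests.

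**How often they might disagree (visit rates assumed).** Visit times were simulated as Poisson, 40,000 men per rate, with blocks from baseline and the Outcomes visit rule required in each of the two study years, laboratory tests ignored. The share meeting the Outcomes rule but not full retention was 5.4%, 9.5% and 11.1% at 2, 3 and 4 visits per year. Requiring the rule in only one 12-month period could only raise these shares; applying the laboratory tests could lower them. The same simulation gave 1.8% to 2.8% in the other direction, but only because it imposed fixed study years, so by the argument above those figures are not used.

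**Clock.** A 2-year window from a visit at month m after baseline ends at month 24 + m, and its fourth block runs from m + 18 to m + 24.
- m = 2: ends at month 26; the fourth block is 20–26, of which 4 of 6 months are observed.
- m = 7: ends at month 31; the fourth block is 25–31, none of it observed.
- m = 9: ends at month 33.
- If the visit precedes baseline, the first block includes time before randomisation.
- A man with no attended visit has no defined window.

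**The case against.** The strongest defence is that the clock may be harmless. The text does not place the initial visit before, at or after randomisation. Assessments at 6, 12, 18 and 24 months from baseline mark out four 6-month blocks, and Couple Dissolution speaks of a 2-year follow-up. If the baseline visit is the anchor, the window matches follow-up and nobody is left out. That reading is plausible, but it is not what the words say, and it fits poorly with men who enter care only later.

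A reader might go further and infer that the clock starts after randomisation, that men who never attend are dropped, and that intent-to-treat is therefore broken, perhaps enough to reverse an effect. The document does not support this. It states intent-to-treat, excludes nobody for non-attendance, and a block count can be zero. Linkage for men out of care has its own measure, timed from baseline. Any sign reversal would rest on invented attendance and retention rates.

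It can also be said that the two measures serve different purposes, a yes/no status and a longitudinal count, and that an article may leave detail to the full protocol. That would answer an omission. Here two conflicting rules are stated for one component of a primary outcome, with no ranking.

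**Conclusion.** The conflict between definitions is established from the text with high confidence, and it alone justifies correction before arms are compared. It runs both ways: through visit pattern in one direction, and through missing laboratory tests in the other. Its frequency in this trial is unknown. The 5.4% to 11.1% range rests on assumed random visits at 2 to 4 per year and leaves out the laboratory requirements.

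The clock element holds with moderate confidence and conditionally. The start is not anchored to randomisation. It could undermine the intent-to-treat comparison if it falls at a visit the intervention can influence, or if men with no visit are excluded. The exposure lies mainly with men out of care at baseline, whose number is not given. For any start after baseline, the overrun past month 24 is arithmetic.

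**What to change.** Name one retention definition as the component of the primary outcome, word it identically in Outcomes and Statistical Analyses, and label the other a secondary measure. Fix the choice before any comparison between arms.

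If the block measure is chosen, define four fixed blocks from the date of randomisation (0–6, 6–12, 12–18 and 18–24 months). Keep every randomised HIV-positive partner in the denominator, and score an observed block without a visit as zero. Blocks not observed because a man left the study should be handled by the stated missing-data approach and not silently counted or dropped.

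The cost is wording in two sections. Visit dates are needed under either definition, so no new data collection follows from the block version.

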#### Dyadic Characteristics

The four elements of Lewis’ model [57] (*predisposing factors of couples*, *partner’s transformation of motivation*, *process of communal coping*, and *use of communal coping*) are referred to as *dyadic characteristics*. In a recent RCT of CHTC, scales were developed to capture these constructs; all scales showed strong reliability, and evidence for construct validity was obtained for all scales [60]. In this intervention, each of the scales is collected in the baseline and follow-up surveys.

#### Predisposing Factors

Predisposing factors of couples uses several scales to measure this element. *Perceived Severity of HIV Scale:* this construct involves the perception of the personal, psychosocial, and physical consequences of a particular health threat. A total of 13 items were developed that crossed the three pertinent consequences of a particular health threat: personal, psychosocial, and physical. *Preferences for General Lifestyle Outcomes Scale*: this construct is defined as the degree to which interacting partners agree about the shared or joint outcomes in their relationship, which is composed of two subscales (*Preferences for General Lifestyle Scale* and *Preferences for Sexual Health Outcomes Scale*). The *Preferences for General Lifestyle Scale* includes six outcomes, including diet, nutrition, and social activities. *Preferences for Sexual Health Outcomes Scale* relates to sexual health (eg, reducing one’s risk for HIV). In addition, scales to measure other predisposing factors of couples are proposed for inclusion. *Conflict Style* determines how respondents typically handle conflict in their relationships, so the Conflict Style Inventory will be included [61]. *Communication Style* is measured with the Communication Patterns Questionnaire Constructive Communication subscale [62]. Finally, *Problem-Solving Skills* are measured with the adherence problem solving/readiness scale [63].

#### Partner’s Transformation of Motivation

In a recent RCT of CHTC, two measures were developed: ability of the participants to respond (1) cognitively and (2) emotionally to the health threat [20]. The scale for emotional response includes whether the respondent reports being fearful, nervous, or anxious about HIV. The scale for cognitive response includes whether the respondent reports understanding the risks of HIV transmission associated with being in a sero-discordant relationship, and the risks associated with outside sex partners.

#### Process and Use of Communal Coping

Several scales are used to measure this element. The *Outcome Efficacy to Reduce HIV Threat Scale* discusses how communal coping involves couples working together and making decisions to reduce the health threat. Three subscales were created to capture the full range of outcome efficacy related to these three processes of communal coping. For the first subscale, *Joint Effort*, the stem, “My partner and I believe that ‘working together’ versus on our own is an effective strategy” is used. For the second subscale, *Communication*, the stem, “Communicating with my partner is an effective strategy for” is used. For the third subscale, *Planning and Decision-making*, the stem, “My partner and I making decisions together rather than separately is an effective strategy” is used. The items for each of the three subscales were the same as the items used for the *Preferences for Sexual Health Outcomes Scale*. The *Couple Efficacy to Reduce HIV Threat Scale* defines couple efficacy as a couple’s confidence that together they can engage in communal coping efforts. The study also assesses the occurrence of violence within the relationship using the Conflict Tactics Scale Revised [64] to assess both perpetration and experience of IPV.

### Statistical Analyses

The analysis employs an intent-to-treat analysis design. The percentage of HIV-positive individuals who achieve viral suppression and report being fully engaged in care will be compared across arms, using Chi-square tests for significant difference. Retention in care is measured as the number of 6-month blocks during which at least one clinic visit was attended over the 2-year period following an initial attended visit; the percentage of HIV-positive individuals who report full retention in care (one clinic visit during each 6-month block) and the number of 6-month blocks during which care was received will be compared across study arms, using the appropriate tests for statistical significance. The capability of the intervention to yield longer-lasting effects in adherence endpoints over time will be examined. The visual analog scale data over the course of the study, at baseline and follow-up, will be analyzed using generalized linear models (GLMs) with properly-chosen (based on the distribution of dependent variables) link functions to analyze longitudinal adherence outcome data. The GLMs will be estimated using generalized estimating equations (GEE) with robust standard error estimates, which provide an extension of regression analyses to the cases of correlated or repeated observations and allows for inclusion of both categorical and count-dependent variables, and for appropriate modeling of covariance structures when observations are correlated across time. With appropriate link functions, GLMs can readily handle dependent variables with normal distributions, dichotomous outcomes, count data (Poisson distribution), and over-dispersed or zero-inflated count data (negative binomial models). The models will include the dyadic characteristics scales to examine the extent to which adherence is shaped by relationship functioning.

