### Participants

Eligible participants are cis-gender male couples in which: (1) two men report having been in a relationship with each other for greater than one month, with a relationship defined as, “having a male partner who you are committed to above all others”; (2) both men are aged over 18 years; (3) individuals have lived in the Atlanta, Boston, or Chicago metro areas for greater than 3 months; (4) participants reported no recent history (in the past 12 months) of IPV or coercion; and (5) an HIV sero-discordant relationship exists, in which both partners have disclosed their sero-status to each other. Prevalent HIV sero-positive statuses are self-reported and are not confirmed by study staff.

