### Data Collection

After a couple gives informed consent, but before the couple is randomized to either the intervention or control group, each member of the couple is given a baseline survey. This survey is approximately 60-90 minutes long and collects data on demographics, relationship characteristics, sexual history, HIV care, and HIV prevention. In addition to survey data, biological samples are collected: STI testing, ART/preexposure prophylaxis (PrEP) drug adherence testing, and viral load testing. At the Boston site, however, STI testing is not conducted due to budgeting constraints.

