### Randomization

Upon individual completion of the check-in survey by both partners, couples are randomized to either the control arm (Individual Counseling) or the intervention arm (Couples Counseling). The treatment assignments are generated with the use of one pseudo-random number generator across all three study sites. The randomization process generates a random number between 0 and 100. If given an odd number, the couple is placed in the control treatment group; if given an even number, the couple is placed in the intervention treatment group.

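### The primary test of viral suppression and full engagement in care ignores baseline status that is already collected: valid, but it gives up precision and leaves chance imbalance uncorrected

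*Protocol article*

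**What the plan says.** - **Primary outcomes** (Outcomes): "The primary outcomes are the HIV-positive partner’s engagement in HIV care and his achievement of viral suppression". There is one HIV-positive partner per couple, so the observations are independent.
- **Primary test** (Statistical Analyses): the percentages suppressed and fully engaged "will be compared across arms, using Chi-square tests for significant difference". No covariate or stratum is named. Full retention and the count of 6-month blocks are left to whichever tests are appropriate, so the Chi-square is fixed only for suppression and full engagement.
- **Baseline data** (Data Collection): before randomization the survey "collects data on demographics, relationship characteristics, sexual history, HIV care, and HIV prevention", and the samples cover "STI testing, ART/preexposure prophylaxis (PrEP) drug adherence testing, and viral load testing". Biomedical Measures adds: "For HIV-positive partners, viral load and ART levels are measured at each study assessment".
- **Eligibility** (Participants): five criteria, the last being that "an HIV sero-discordant relationship exists, in which both partners have disclosed their sero-status to each other". None concerns viral load, ART use or care status.
- **Mixed baseline status** (Outcomes): linkage is defined for a subset only: "For HIV-positive partners who report no engagement in HIV care at baseline, linkage to care is defined as".
- **Allocation** (Randomization): assignments are "generated with the use of one pseudo-random number generator across all three study sites", by odd or even number. No stratification or blocking is described.

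**The concern.** A man who enters suppressed and stays suppressed counts the same as one who becomes suppressed during the trial. If baseline status predicts later status, part of the outcome variation is explained by a variable that the trial already holds, and an unadjusted 2×2 table treats that part as noise.

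Allocation does not balance baseline status or site by design. If one arm happens to start with more suppressed men, the unadjusted difference carries that gap forward. At stake are power in a trial of moderate size and the credibility of the estimate if the baseline table shows an imbalance.

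**Working it through.** **1. Does the plan adjust the primary comparison elsewhere?** No.
- The GEE models in Statistical Analyses are for longitudinal adherence data on the visual analog scale.
- Race, age and relationship duration are covariates for at-risk sex.
- The adjustment for outside testing belongs to the STI analyses.
- The interaction terms are for moderation.

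**2. Evaluable sample.** From Sample Size: 165 × 0.80 = 132, or 66 per arm. The section gives no control-arm rate, so its 80% power statement cannot be reproduced and is not used here.

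**3. Illustrative scenario.** All rates are assumptions: 70% suppressed at baseline; later suppression, by baseline suppressed/unsuppressed, of 90%/40% in control and 97%/75% in intervention.
- Control overall: 0.7 × 0.90 + 0.3 × 0.40 = 0.75.
- Intervention overall: 0.7 × 0.97 + 0.3 × 0.75 = 0.904.
- Baseline-outcome correlation = (difference between strata) × √(0.7 × 0.3) / √(p(1 − p)).
- Control: 0.50 × 0.458 / 0.433 = 0.53. Intervention: 0.22 × 0.458 / 0.295 = 0.34.

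**4. Power by simulation, two-sided 5%.**

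| Analysis | Power | Type I error |
|---|---|---|
| Chi-square | 65–66% | 5% |
| Adjusted for or stratified by baseline | 75% | 5% |

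**5. What that gain is worth.** Ratio of information = [(1.96 + z of adjusted power) / (1.96 + z of unadjusted power)]². With powers 0.646 and 0.747: [(1.96 + 0.665) / (1.96 + 0.375)]² = 1.26. With 0.66 and 0.75 it is 1.23. So adjustment is worth about 25% more couples.

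**6. Sensitivity.** 132 evaluable, 25% relative increase, Chi-square against a baseline-stratified Cochran-Mantel-Haenszel test; control rates and correlations are assumed.

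| Control rate | Correlation | Chi-square | Stratified |
|---|---|---|---|
| 51% | 0 | 32% | 31% |
| about 70% | 0.14 | 70% | 70% |
| about 70% | 0.39 | 64% | 70% |
| about 53% | 0.45 | 35% | 40% |
| about 53% | 0.65 | 35% | 51% |
| about 70% | 0.65 | 72% | 87% |
| about 35% | 0.66 | 17% | 25% |

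The gain is nil at 0 to 0.14, about 4 to 6 points at 0.39 to 0.45, and 8 to 16 points at about 0.65.

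**7. Chance imbalance.** SD of the baseline difference = √(2 × 0.7 × 0.3 / 66) = 0.080, so P(|difference| > 0.10) = P(|Z| > 1.25) = 0.21. For baseline prevalence from 28% to 70% the figure is 20% to 26%.

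**8. Consequence of an imbalance.** With no true effect and the control rates of step 3, a 10-point baseline gap moves the expected unadjusted difference by 0.10 × (0.90 − 0.40) = 5 points. Among null trials with a gap above 10 points favouring intervention, the Chi-square rejects in about 12%, against 5% for the stratified test. Across assumed correlations of 0.39 to 0.66 the Chi-square figure is 10% to 17%.

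**The case against.** The strongest reply is that nothing is invalid. Randomization makes the unadjusted Chi-square a correct 5% test and the difference unbiased over repeated allocations; chance imbalance is already inside that 5%. This stands, and it limits the point to efficiency and to conditional error once an imbalance has occurred.

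The inputs are also assumptions. The only suppression figure in the document is the national 28% in the Introduction, and clinics are one recruitment route among several. A reader might infer that the outcome will mostly reflect baseline status; the document has no data to show that. The gain could be nil.

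A reader might take 1/(1 − 0.53²) = 1.39 and claim 39% more information. That uses the control-arm correlation alone. The intervention-arm value is 0.34, and the simulated powers support about 25%.

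A reader might also add that the trial is already short of its stated power. That is a separate question and turns on a control rate the document does not give. Results reports 160 couples and 24-month retention above 90%; if 90% holds, 160 × 0.90 / 2 = 72 per arm. The same scenario then gives 70% against 79%, and a gap above 10 points in 19% of trials. The gain is similar.

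Finally, adjusted analyses are often left to an analysis plan. Here, however, the article names the primary test, so adjusting it means changing a stated method rather than supplying an omitted detail.

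**Conclusion.** The point holds as one of efficiency and uncorrected chance imbalance, not of validity. For viral suppression and full engagement in care, the plan fixes an unadjusted test while holding the baseline value of the same outcome, and no other part of the design or analysis makes up for it.

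In the assumed scenario the cost is about 10 points of power, or about 25% of the sample in information; the wider range for a 25% relative increase runs from nothing to about 16 points. A baseline gap above 10 points is expected in roughly one trial in five. The facts about the plan are certain. The magnitude rests on baseline prevalence, control rates and correlations that the document does not state. Adjustment does not by itself secure 80% power at lower control rates.

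**What to change.** For viral suppression and full engagement in care, pre-specify a primary analysis adjusted for baseline status of the same outcome, and preferably for site. Either of these would serve:
- logistic regression, reported as a standardized risk difference or risk ratio with confidence interval; or
- a Cochran-Mantel-Haenszel test stratified by baseline status.

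Apply it at the trial's own primary time point, which Statistical Analyses does not state for this comparison and which should be named in the same place. Keep the Chi-square as a supporting analysis.

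Do not adjust linkage to care for baseline engagement, since it is defined only for men not in care at baseline. Retention counted in 6-month blocks would need a baseline counterpart defined before any such adjustment.

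The cost is a short change of wording, including a definition of baseline full engagement from the survey. Baseline viral load and care data are already collected, so no new data are needed. The change should be fixed before outcomes are compared by arm.
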